#### **4.4.1.3 Reporting of Serious Adverse Events**

##### **Timelines for reporting of SAEs**

Investigators and other study site personnel must inform appropriate Astra Tech representatives of any SAE that occurs during the course of the study within one day (i.e., immediately but no later than the end of the next business day) of when he or she becomes aware of it.

The Astra Tech representative will work with the Investigator to compile all the necessary information and ensure that the appropriate Astra Tech personnel receives a report by day one for all fatal and life-threatening cases and by day five for all other SAEs.

If an AE or ADE becomes a SAE, this and other relevant follow-up information must also be provided to Astra Tech within one day for all fatal and life-threatening cases and by day five for all other SAEs.

The Investigator is responsible for informing the ethics committee of SAEs as per local requirements.

Astra Tech is responsible for informing the regulatory authority of SAEs as per local requirements.

## 4.5 Patient-Reported Outcomes (PROs)

### 4.5.1 Health status questionnaire

#### 4.5.1.1 Methods of assessment

Health status will be measured by means of a validated self reported quality of life questionnaire, i.e. the EQ-5D. The questionnaire will be completed 4 days after surgery and at the check up at 2 months.

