### 2.2 Secondary objectives

The secondary objectives of the study are....

....to observe and compare clinical efficacy by means of postoperative infection rates, use of postoperative antibiotics, length of hospital stay and health status for patients transfused with Sangvia® blood, no blood and/or allogeneic blood.

....to observe and compare clinical efficacy by means of systemic postoperative haemoglobin levels for patients transfused with Sangvia® blood, no blood or allogeneic blood.

....to collect details in health care utilisation (medications, in-patient service use, blood management) that would allow a calculation and comparison of cost-consequences applying either alternative in the blood management and from the perspective of the payer

....to observe and compare safety by means of adverse events, highlighting renal failures and events potentially related to transfusion, body temperature and other clinical complications for patients transfused with Sangvia® blood, no blood or allogeneic blood.

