### **Post-operative follow-up**

#### 3 ( $\pm$ 1) hours after end of surgery

- Surgery stop time will be registered in the CRF
- The estimated intra-operative and post-operative blood loss volumes will be registered in the blood loss log.
- Any allogeneic and/or autologous blood transfusions will be registered in the allogeneic and/or the autologous transfusion logs.
- The Sangvia® postoperative drain (test group) and the Bellovac drain (control group) connection time will be registered.
- Venous blood sample/s will be taken from each subject before return of post-operative autologous blood if applicable for analyses of Hb, Hct/EVF,  $\text{Na}^+$ ,  $\text{K}^+$ , TPC, CRP, LPC, creatinine and Glomerular Filtration Rate (GFR)/Creatinine Clearance ( $\text{C}_{\text{Cr}}$ ).
- For the patients randomized to the Sangvia® treatment group postoperative blood salvage will be stopped, returned and the kit disconnected within 6 hours after activation. The drain will remain connected until the first post-operative day. In total, the transfusion volume of 2500 ml must not be exceeded when combining the intra- and postoperatively collected autologous blood.
- Drainage will continue in both treatment groups.
- Any allogeneic and/or autologous blood transfusions will be registered in the allogeneic and/or the autologous transfusion logs.
- Presence of SIRS will be evaluated.

- Vital signs (blood pressure, body temperature and heart rate) will be registered.
- Any additional adverse events and/or medications will be registered in applicable logs.
- Clinical signs or symptoms of general and/or wound infection will be registered.

Day 1 - first post-operative morning, 24 ( $\pm 6$ ) hours after end of surgery

- Venous blood sample/s will be taken from each subject 24 hours after end of surgery for analyses of Hb, Hct/EVF,  $\text{Na}^+$ ,  $\text{K}^+$ , TPC, CRP, LPC, creatinine and Glomerular Filtration Rate (GFR)/Creatinine Clearance ( $\text{C}_{\text{Cr}}$ ).
- The estimated additional post-operative blood loss volume will be registered in the blood loss log, if applicable.
- Drainages in both treatment groups will be removed.
- Any additional allogeneic blood transfusions will be registered in the allogeneic transfusion log.
- Presence of SIRS will be evaluated
- Vital signs (blood pressure, body temperature and heart rate) will be registered.
- Any additional adverse events and/or medications will be registered in applicable logs.

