- Clinical signs or symptoms of general and/or wound infection will be registered.

Day 2 – 48 ( $\pm 6$ ) hours after end of surgery

- Venous blood sample/s will be taken from each subject 48 hours after end of surgery for analyses of Hb, Hct/EVF,  $\text{Na}^+$ ,  $\text{K}^+$ , TPC, CRP, LPC, creatinine and Glomerular Filtration Rate (GFR)/Creatinine Clearance ( $\text{C}_{\text{Cr}}$ ).
- Any additional allogeneic blood transfusions will be registered in the allogeneic transfusion log.
- Vital signs (blood pressure, body temperature and heart rate) will be registered.
- Any additional adverse events and/or medications will be registered in applicable logs.
- Clinical signs or symptoms of general and/or wound infection will be registered.

Day 3 – 72 ( $\pm 6$ ) hours after end of surgery

- Any additional allogeneic blood transfusions will be registered in the allogeneic transfusion log.
- Vital signs (blood pressure, body temperature and heart rate) will be registered.
- Any additional adverse events and/or medications will be registered in applicable logs.
- Clinical signs or symptoms of general and/or wound infection will be registered.

Day 4 – 96 ( $\pm 6$ ) hours after end of surgery

- Venous blood sample/s will be taken from each subject 4 days after end of surgery for analyses of Hb, Hct/EVF,  $\text{Na}^+$ ,  $\text{K}^+$ , TPC, CRP, LPC, creatinine and Glomerular Filtration Rate (GFR)/Creatinine Clearance ( $\text{C}_{\text{Cr}}$ ).
- Any additional allogeneic blood transfusions will be registered in the allogeneic transfusion log.
- Vital signs (blood pressure, body temperature and heart rate) will be registered.
- Any additional adverse events and/or medications will be registered in applicable logs.
- Clinical signs or symptoms of general and/or wound infection will be registered.
- The patients will fill out a health status questionnaire.

Discharge

An assessment at discharge will be performed if discharge occurs later than 4 days after surgery.

- Any additional allogeneic blood transfusions will be registered in the allogeneic transfusion log.
- Vital signs (blood pressure, body temperature and heart rate) will be registered.
- Any additional adverse events and/or medications will be registered in applicable logs.
- Clinical signs or symptoms of general and/or wound infection will be registered.

Month 2 – 5-12 weeks after end of surgery

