| Health status questionnaire                                   |                        |                            |                                                                                   |                                      |                                      |                                      |                                      | X                   | X                          |

Hb = Haemoglobin concentration (g/dl)

Hct/EVF = Haematocrit/Erythrocyte Volume Fraction (%)

Na+ = Sodium (mmol/l)

K+ = Potassium (mmol/l)

TPC = Thrombocyte Particle Concentration (10^9/l)

LPC = Leukocyte Particle Concentration (10^9/l) with applicable differentiation in percentage of neutrophils, eosinophils, basophils, lymphocytes, monocytes and macrophages.

CRP = C-reactive protein concentration (mg/l)

Creatinine = Serum creatinine ( $\mu$ mol/l), GFR = Glomerular Filtration Rate, CCr = Creatinine Clearance (ml/min/1.73m^2)

SIRS = systemic inflammatory response syndrome, i.e. two or more of the following

- Body temperature  $>38^{\circ}\text{C}$  or  $<36^{\circ}\text{C}$
- Heart rate  $> 90$  beats/minute
- Respiratory rate  $> 20$  breaths/minute or PaCP2  $< 32$ mmHg
- LPC  $> 12 \times 10^9/\text{l}$  or  $< 4 \times 10^9/\text{ml}$  or 0.1% immature neutrophils

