## 3.4 Treatments

### 3.4.1 Identity of investigational product and comparators

The investigational product is the CE-marked Sangvia® Blood Salvage System. The system consists of an intra-operative set, a post-operative set and vacuum tubing that enable collection, filtration and transfusion of intra-operative and post-operative blood.

[figure not shown]

The recommended user instructions for the Sangvia® Blood Salvage System should be followed for set-up, blood collection and reinfusion.

In summary, the collection canister is connected to a suction source with the recommended suction pressure of 100 mmHg (maximum 150 mmHg is allowed) and a suction tip is connected to the inlet tubing of the system. The collection unit is placed lower or at the same height as the operation table and an anticoagulant drip is connected to the system (ACD-A, sodium citrate or CPD) with the recommended ratio of 1:7 (approximately 20 drips per minute). The blood is filtered from larger debris, cement and bone particles by a macro filter of 200µm when collected in the chamber. The upper compartment of the collection unit has a maximum volume of 700 ml and the lower compartment has a maximum volume of 500 ml. When blood is being emptied to the transfusion bag the opening between the upper and the lower compartments should be closed. The blood is filtered from small particles by a micro filter before reinfusion. The reinfusion is initiated when 500 ml blood have been collected or at the end of surgery. Blood transfusion should be completed within 6 hours of the start of collection. Post-operative collection and transfusion will follow after surgery. The post-operative set is set-up and used according to the recommended user instructions. As for the intra-operative collection phase blood transfusion must be completed within 6 hours from start of collection during the post-operative phase. The reinfusion of the post-operatively collected blood may start either when the blood has passed 500 ml in the lower chamber or at the end of the 6 hour collection period. Not more than 2500 ml intra- and/or postoperatively collected blood in total should be transfused to the patients.

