#### 4.5.1.2 Derivation or calculation of variable

Applicable scores and results from the questionnaire will be analyzed and presented according to user instructions from the provider. The results from the two treatment groups at day 4 and month 2 as well as the change between the two assessments will be compared.

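### The first EQ-5D is at day 4 in the protocol text but at discharge in Table 1, and with no pre-operative form the planned change score runs between two post-treatment values

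*Protocol*

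**What the plan says.** Health status is part of a secondary efficacy objective. Protocol section 2.2 sets out to compare "length of hospital stay and health status for patients transfused with Sangvia® blood, no blood and/or allogeneic blood".

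On timing, section 4.5.1.1 says "The questionnaire will be completed 4 days after surgery and at the check up at 2 months". In the visit-by-visit description in section 3.1, the line "The patients will fill out a health status questionnaire" stands under Day 4 and under Month 2, and not under Screening, Preoperative or Discharge. Section 4.5.1.2 plans to compare the two groups at day 4 and at month 2, and adds that the change "as well as the change between the two assessments will be compared" (the last words of that sentence).

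Table 1 differs. Its row "Health status questionnaire" has a mark under Discharge and one under Month 2; Screening, Pre-op and Day 4 are empty.

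The discharge visit is conditional in section 3.1: "An assessment at discharge will be performed if discharge occurs later than 4 days after surgery".

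**The concern.** Two things need attention.

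First, the protocol gives sites two instructions for the first form and does not say which prevails. Sites following the text collect it at about 96 hours. Sites following Table 1 collect it on a day that varies with length of stay, which is a secondary outcome and could differ between arms. Pooling the two mixes different stages of recovery in one variable. Patients who go home early are also poorly covered. Under Table 1 combined with section 3.1, anyone discharged by day 4 has no discharge assessment at which to complete the form. Under the text, nothing says what happens when discharge comes before day 4.

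Second, with no pre-operative form, the planned change is not a change from baseline. Both scores follow the randomised treatment, so a between-arm difference in change does not measure benefit: an early gain for one arm is subtracted from that arm's result.

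**Working it through.** **Timing, side by side**

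| Place in protocol | Screening / pre-op | Day 4 | Discharge | Month 2 |
|---|---|---|---|---|
| Section 3.1 visit lists | no | yes | no | yes |
| Section 4.5.1.1 | no | yes | no | yes |
| Section 4.5.1.2 (comparisons) | no | yes | no | yes |
| Table 1 | no | no | yes | yes |

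The Table 1 row has all nine visit cells and its marks line up with Discharge and Month 2, so damage in reading the table is an unlikely explanation. Text and table disagree at both Day 4 and Discharge.

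**Is the first form after treatment?** Section 3.4.1: "The reinfusion is initiated when 500 ml blood have been collected or at the end of surgery". Section 3.1: "postoperative blood salvage will be stopped, returned and the kit disconnected within 6 hours after activation". Both precede day 4, so the first EQ-5D always follows the randomised treatment.

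**What the change contrast estimates.** Let d4 and d2 be the between-arm differences (Sangvia minus control, higher is better) at day 4 and month 2. The difference in mean change is d2 - d4. Illustrative values, in SD units and not from the documents:

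| d4 | d2 | contrast in change |
|---|---|---|
| 0 | 0.3 | 0.3 |
| 0.2 | 0.3 | 0.1 |
| 0.3 | 0.3 | 0.0 |
| 0.3 | 0.1 | -0.2 |
| 0.3 | 0 | -0.3 |

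A benefit present from day 4 and fully kept gives zero. A benefit that fades gives a negative value.

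**Variance of the change.** With equal variances and day-4/month-2 correlation r, the variance of the change relative to the month-2 score is 2(1 - r): 1.4 at r = 0.3, 1.0 at r = 0.5, 0.6 at r = 0.7. The change may be noisier or less noisy than month 2, depending on r.

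**Precision lost without a baseline.** With baseline/month-2 correlation r, a covariate-adjusted comparison has 1 - r² of the unadjusted variance:
- r = 0.3: 1 - 0.09 = 0.91, a saving of 9%
- r = 0.5: 1 - 0.25 = 0.75, a saving of 25%

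To put this in terms of power, the protocol's planned size is needed. It gives no EQ-5D calculation. Its figure for the primary variable reproduces: (1.96 + 1.2816)² × 4 × 0.14 × 0.86 / 0.14² = 258.2, against a stated 260, or 130 per arm before the drop-out allowance. With 130 per arm and an assumed month-2 effect of 0.3 SD, power is Φ(0.3 × √(130/2) - 1.96) = Φ(0.459) = 68% unadjusted. Dividing 0.3 by √0.91 or √0.75 gives 72% or 80%.

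**The case against.** The best case for the plan is as follows. Three places in the text agree on day 4 against one table row, so the likely repair is to move one mark. If the text is followed, every patient's form is due at 96 (±6) hours and does not depend on length of stay. The groups are compared at day 4 and at month 2 as well as on the change, so an early advantage stays visible, and nothing makes the change the leading EQ-5D analysis. Read with the other two, it describes one arm catching up. Randomisation, stratified by clinic and by primary or secondary surgery, protects both single-time comparisons without a baseline.

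Most of this stands, and it rules out some stronger readings that a reader might infer:

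- **That the day-4 score is already affected by treatment.** The documents show only that it is measured after treatment and so is open to an effect.
- **That early-discharged patients certainly have no first form.** Day 4 in section 3.1 is not limited to in-patients, and the form is self-reported. The protocol leaves the case open, and gives no share of patients discharged by day 4.
- **That the missing baseline biases the results.** It costs precision.
- **That the change score is necessarily noisier.** That holds only for r below 0.5.

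The precision gain also applies to a covariate-adjusted analysis. The Wilcoxon rank sum test planned in sections 6.2 and 6.4 would not deliver it as it stands.

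What the objection does not remove is the conflicting instruction, the absence of any rule for discharge before day 4, and a planned between-arm comparison of a quantity that does not measure benefit. Nor can these be left to a statistical analysis plan: no analysis can recover a pre-operative form that was never collected or a first form taken at inconsistent times.

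**Conclusion.** The point holds in a limited form. The contradiction between Table 1 and sections 3.1, 4.5.1.1 and 4.5.1.2 is plain on the page. If Table 1 is followed, the first EQ-5D depends on length of stay, and patients discharged by day 4 lack an assessment at which to give it. That the change contrast equals the month-2 effect minus the day-4 effect is arithmetic and needs no assumption; whether it would in fact be zero or negative depends on effects that the documents do not give.

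The missing baseline is a matter of efficiency: 9-25% of variance under assumed correlations of 0.3-0.5 and a covariate-adjusted analysis. The day-4 and month-2 comparisons remain unbiased through randomisation. EQ-5D is a secondary variable, so the primary conclusion on allogeneic transfusion is untouched. The change is worth making because it is cheap and concerns a named efficacy objective.

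**What to change.** 1. Correct Table 1 so that the first post-operative EQ-5D is at Day 4, and state in sections 3.1 and 4.5.1.1 that it is completed on the day of discharge if that is earlier. A full discharge assessment for every patient is not needed.
2. Add one EQ-5D at the screening visit, before allocation.
3. In section 4.5.1.2, compare the arms at day 4 and at month 2, each adjusted for the pre-operative score, and name the adjusted method in section 6.4, which now lists only rank tests for continuous variables.
4. Label the day-4-to-month-2 change as descriptive, not as evidence of a treatment effect. If a pre-operative form cannot be collected, keep the unadjusted comparisons at each time point and still label the change descriptive.

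While Table 1 is open, align the Month 2 window too: section 3.1 counts 5-12 weeks from the end of surgery, Table 1 from discharge.

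Cost: one extra short questionnaire per patient at an existing visit, a CRF change, and an amendment handled under section 7.4.

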#### 4.5.1.2 Derivation or calculation of variable

Applicable scores and results from the questionnaire will be analyzed and presented according to user instructions from the provider. The results from the two treatment groups at day 4 and month 2 as well as the change between the two assessments will be compared.

## 4.6 Health Economic measurements and variables

### 4.6.1 Health care utilisation

#### 4.6.1.1 Methods of assessment

Health care utilisation will be measured by length of hospital stay, type of care facility during hospital stay, use of medications, bank blood and the Sangvia® treatment.

#### 4.6.1.2 Derivation or calculation of variable

Values for length of hospital stay, type of care facility, use of medications, bank blood and the Sangvia® treatment will be derived from the results from the current study. Unit costs will not be applied within the study.

## 4.7 Volume of blood sampling and handling of biological samples

The total volume of blood that will be drawn from each subject in this study is as follows:

**Table 2**                      **Volume of blood to be drawn from each subject**

| Sampling time/Visit No.          | Sample volume (mL) | No. of samples | Total volume (mL) |
|----------------------------------|--------------------|----------------|-------------------|
| 1. Screening/Pre-op              | 5 ml               | 2              | 10 ml             |
| 4. 3 hours after end of surgery  | 5 ml               | 2              | 10 ml             |
| 5. 24 hours after end of surgery | 5 ml               | 2              | 10 ml             |
| 6. 2 days after surgery          | 5 ml               | 2              | 10 ml             |
| 8. 4 days after surgery          | 5 ml               | 2              | 10 ml             |
| Total                     |                    | 10             | 50 ml             |

## 4.7.1 Analysis of biological samples

### 4.7.1.1 Clinical chemistry samples

Blood markers related to routine safety monitoring after surgery will be analysed, i.e. haemoglobin concentration (g/dl), haematocrit/Erythrocyte Volume Fraction (%), sodium (mmol/l), potassium (mmol/l), Thrombocyte Particle Concentration ( $10^9/l$ ), Creatinine ( $\mu\text{mol/l}$ ) and Glomerular Filtration Rate (GFR)/Creatinine Clearance ( $C_{Cr}$ ) ( $\text{ml/min/1.73m}^2$ ).

Analyses will be made according to the schedule below:

|                              | Screening/
Pre-op (1) | 3 hours
post-op
(4) | 24 hours
post-op
(5) | 2 days
post-op
(6) | 4 days
post-op
(8) |
|------------------------------|--------------------------|---------------------------|----------------------------|--------------------------|--------------------------|
| Hb                           | X                        | X                         | X                          | X                        | X                        |
| Hct/EVF                      | X                        | X                         | X                          | X                        | X                        |
| TPC                          | X                        | X                         | X                          | X                        | X                        |
| LPC                          | X                        | X                         | X                          | X                        | X                        |
| Na                           | X                        | X                         | X                          | X                        | X                        |
| K                            | X                        | X                         | X                          | X                        | X                        |
| Creatinine,
GFR/ $C_{Cr}$ | X                        | X                         | X                          | X                        | X                        |
| CRP                          | X                        | X                         | X                          | X                        | X                        |

Hb, Hct/EVF, TPC, LPC in one EDTA container, 5 ml blood..

$\text{Na}^+$ ,  $\text{K}^+$ , CRP and creatinine should be taken in one gel container (e.g. Hettich Lab Instruments), 5 ml blood.

